#### Primary objectives

To determine baseline self-care (self-care maintenance, self-care management and self-care confidence) in patients with CHF discharged from Imam Ali hospital (Iran) from August 2010 to June 2012.

To measure the scores relating to self-care (self-care maintenance, self-care management and self-care confidence) in each of the three arms of the study, two months after applying interventions.

To compare self-care maintenance, self-care management and self-care confidence among groups I and, II, I and III, II and III.

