### Outcomes

The self-care components including self-care maintenance, self-care management and self-care confidence would be the main outcome variables of the study. These outcomes will be assessed before intervention and two months after intervention. The Persian version of the self-care chronic heart failure index V 6.2 (pSCHFI) scales is used to evaluate self-care components in three groups of study. The SCHFI uses a quantitative, ordinal, self-report and performance-rating scale (Riegel et al.
2009). Both SCHFI and pSCHFI include three scales with 22 questions–10 questions for self-maintenance, six for self-management and six for self-confidence. Each sub-scale is standardized to a possible score of zero to 100. In Persian version of SCHFI, in comparison with the original SCHFI, some grammatical changes had been made and a few words had been deleted or added, however none of those modifications did not change the meaning of the questions. For example, we inserted the phrase "How routinely do you…" at the beginning of many questions of the Self-maintenance sub-scale, instead of using only one sentence at the beginning of subscale, as used in the original SCHFI. In addition, item 4, "Do some physical activity?" was changed to "Do you routinely do your normal life activities such shopping and cleaning?" (Riegel et al.
2009; Siabani et al.
2014).

In order to obtain demographic data and personal health information- as the secondary outcomes-, an investigator-constructed questionnaire has been also administered that included 13 questions about age, sex, living status (with whom they live), smoking, co-morbidities (e.g. hypertension), duration of heart failure, and the number of times a patient had been admitted to hospital due to CHF symptoms from diagnosis CHF. This information will be used to evaluate the likely association between self-care scales and personal characteristics. Data collected by three experienced trained nurses and through interviewing have been conducted at the patient’s home or hospital, according to participant preference, before intervention and two months after intervention.

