### Sample size

According to the following formula and information received from another study of a similar design (Riegel et al.
2009), it was expected the mean increase in self-care would be about 22 units (d = 22).

Hence to have a power of 90% (σ =40, d = 22, Z α/2 = 1.96, Z β =0.1) minimum 60 participants were needed for each group.

Considering a non-response rate of 15%, the sample size for each group would be 60, and total of 180 participants. However, according expert opinions, all 231 patients who had completed the primary interviews conducted to obtain the baseline data, and agreed with remaining in the study were considered to participate in the RCT, therefore, each group would be included 77 patients (Figure 
1).

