### Statistical methods

SPSS version 21 and SAS will be used to analyse data. Using descriptive analysis for descriptive data, analytic biostatistics analysis (e.g. ANOVA, independent t-test and paired t-test) for assessing differences (between two groups, among three groups and before and after for each group) will be applied. Regression models will be used to explore associations between predicting factors (e.g. age, gender and education) and self-care scales, and also association between the effectiveness of each strategy and personal characteristics will be used. We will present frequencies and examine the expected associations between different variables to obtain answers for our research questions and hypothesis. T-tests will be used for continuous and normally distributed variables (e.g. self-care maintenance in terms of gender), chi-squared for nominal variables and other proportions (e.g. age group, sex), and multivariate generalized linear regression will be used for detecting associations between outcomes (e.g. self-care management) and explanatory variables (e.g. gender, education and disease duration). Non-parametric tests (e.g., Wilcoxon rank test and Median test) will be used when variables are found not to be normally distributed.

A summary of the interventional strategies is presented in the Table 
1.

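### The primary objectives fix nine unranked comparisons, but the sample size covers one; tested at 5% each without a gate, the chance of at least one false positive is about 19% to 32%

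*Protocol article*

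**What the plan says.** Under Primary objectives, the third objective is "To compare self-care maintenance, self-care management and self-care confidence among groups I and, II, I and III, II and III". Under Outcomes, all three scales have equal standing: "The self-care components including self-care maintenance, self-care management and self-care confidence would be the main outcome variables of the study". No scale and no contrast is placed first in either section.

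Statistical methods lists ANOVA, independent t-tests and paired t-tests side by side, for differences "between two groups, among three groups and before and after for each group". It gives no order, no condition linking the ANOVA to the pairwise tests, and no significance level.

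Sample size uses one effect ("it was expected the mean increase in self-care would be about 22 units (d = 22"), one standard deviation of 40 and an undivided Z α/2 of 1.96. It concludes that "minimum 60 participants were needed for each group". In the end 231 patients were randomised, 77 per group.

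**The concern.** The objectives and the sample size describe different trials. The objectives make nine comparisons primary. The calculation protects one of them, on an unspecified self-care score, at two-sided 5%. Nothing states which of the nine results would support the hypothesis in the Aim section.

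If all nine are tested at the level used for sizing and read on an equal footing, the 5% in the calculation is not the error rate of the trial's overall conclusion. The 90% power does not carry over either once a stricter level is used to restore the error rate.

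**Working it through.** **Inputs.** From Sample size: difference 22, SD 40, Z α/2 = 1.96, power 90%, non-response 15%, 77 per group. From Primary objectives and Outcomes: three scales, three contrasts. Assumed, because the article does not give it: the correlation between scales, varied from 0 to 0.9.

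**The plan's own figure.** The two-group formula gives n = 2 × [40 × (1.96 + 1.2816) / 22]² = 69.5, so 70 per group, not 60. The article prints 0.1 for Z β, but that is β; the normal quantile for 90% power is 1.2816. With 60 per group, power is 85.4%. With the 77 allocated it is 92.7%, or 88% if 15% are lost (77 × 0.85 ≈ 65). Sizing is therefore adequate or nearly so for one comparison. The mismatch in the 60 is a separate matter.

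**Count.** 3 scales × 3 contrasts = 9 primary comparisons.

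**Error over the nine.** Under the global null each arm has a standardised mean m, each contrast is z = (m_a − m_b)/√2, and a test is significant if |z| > 1.96. The simulation used 400,000 replicates and kept the correlation that arises because contrasts share an arm.

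- One scale, three ungated pairs: 12.2%.
- Three uncorrelated scales: 1 − (1 − 0.122)³ = 32.3%, which the simulation matches.
- Nine independent tests would give 1 − 0.95⁹ = 37.0%, but contrasts among three arms cannot be independent.

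| Between-scale correlation (assumed) | Any of nine, ungated, either direction | False claim that I or II beats control on any scale | ANOVA gate at 5% per scale | I–II contrast only, three scales |
|---|---|---|---|---|
| 0 | 32% | 13% | 14% | 14% |
| 0.5 | 28% | 11% | 13% | 13% |
| 0.7 | 25% | 10% | 11% | 11% |
| 0.9 | 19% | 7% | 8–9% | 8% |

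The benefit column should be set against 2.5%, the chance that one two-sided 5% test errs in the favourable direction. The other columns compare with 5%.

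**A fixed order of scales.** Suppose each scale is opened by a significant global test on the one before, and both strategies truly beat control by 22 units on every scale (SD 40, 65 per arm). The I–II null is then true on all three scales and can be tested three times. The simulated chance of a false I–II finding is 13% (correlation 0), 12% (0.5), 10% (0.7) and 8% (0.9). In the same setting, one primary scale with the global test first gives 5%, and the global-then-pairwise procedure at 0.0167 per scale gives 3% to 5%.

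**Power at 65 per arm.** 22 / (40 × √(2/65)) = 3.135.

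- At 0.05: Φ(3.135 − 1.960) = 88%.
- At 0.05/3 = 0.0167: Φ(3.135 − 2.394) = 77%.
- At 0.05/9 = 0.0056, the first Holm step over nine: Φ(3.135 − 2.773) = 64%.

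Requiring the global test as well lowers the first figure to about 85% if the third arm equals one of the two compared, and to about 80% if it lies midway. The second figure falls to about 73% and 66%.

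**The case against.** Testing order and multiplicity rules often sit in a statistical analysis plan, which is not shown, and this is a condensed article. That stands for the missing adjustment rule, which is not the point here. The point rests on what the article does fix: nine primary comparisons without rank, and a sample size at an undivided 5%. A later plan could add an adjustment, but the sizing would still be for one test.

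The 5% level for each test is inferred from the sample size. That also stands, and it is a condition on every figure above.

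A reader might infer that one significant result out of nine would be reported as effectiveness. The text contains no such rule. The Aim section gives one hypothesis, that volunteers are at least as effective as professionals, and no criterion for judging it. The 19% to 32% is thus the chance of some false positive in either direction, including results unfavourable to education. It is not the chance of a false claim of benefit over control, which is 7% to 13%.

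A reader might also count eighteen tests by adding the before-after test in each arm on each scale. Those nine tests appear only in Statistical methods, are not listed as primary objectives, and are not in the figures.

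Finally, the ANOVA could be read as a gate, or the contrasts as separate questions that need no joint control. The text does not specify a gate. With one, or with the I–II contrast alone, the error still exceeds 5%, because three unranked main scales remain.

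**Conclusion.** The concern holds in this conditional form. Nine unranked primary comparisons are set against a sample size for one. With ungated two-sided 5% tests and no true effects, the chance of at least one false positive is about 32%, 28%, 25% and 19% at between-scale correlations of 0, 0.5, 0.7 and 0.9. The test level is inferred and the correlations are assumed. The more favourable readings examined lower the figure, but none reaches the nominal level. This should be corrected; it does not invalidate the design.

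**What to change.** Before outcome data are examined, choose one of these and record the date of the choice:

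- **(a) One primary scale.** Do the three-arm global test at 5%, and the three pairwise tests at 5% only if it is significant. For exactly three arms this controls the error. Label the other two scales and all before-after tests secondary or exploratory.
- **(b) Three primary scales.** Run that same procedure within each scale at 0.05/3 = 0.0167, or apply Holm over all nine p-values.

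Do not use a fixed order of scales opened by the global test alone, since it leaves the I–II contrast uncontrolled. State the power at the level used, with the effect of any gate.

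The cost is mainly wording. Under (a), two scales lose primary status. Under (b), pairwise power for 22 units falls from about 88% to 77% with 65 evaluable per arm, before the further loss from the global test, which is largest when the third arm lies midway. The Payments section describes the two-month interviews in the past tense, so data may already exist. If so, the authors should say whether anyone had seen results by group when the choice was made. If results had been seen, option (b) is easier to defend, because it does not require picking a scale.

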#### Secondary objective

To explore the personal characteristics such as age and gender of study subjects.

To explore the health-related factors such as duration of CHF, number of admissions for CHF, and comorbidities (e.g. diabetes) in study subjects.

To determine the association between each personal factor (e.g. education and age) that might influence the efficacy of interventional strategies.

## Methods

### Trial design

This study is an ongoing three-arm randomised controlled trial aiming to compare a new educational strategy involving community health volunteers (CHVs) with health-professional-based educational strategy, and a control group received standard care without educational intervention. Self-care skill scales will be assessed and compared in three groups of patients with heart failure.

### Participants and setting

Two hundred thirty one patients above 18 years of age, who had been admitted to hospital at least once with CHF during last two years, but not in last two months, were recruited to participate in the study. Those who had CHF of New York Heart Association Class (NYHA) functional class II or III, and did not have cognitive problem were eligible for inclusion in this study. NYHA class IV was excluded because we excluded people with any severe mental or physical disability preventing people of self-care activities. Also, we excluded patients in class I, due to being asymptomatic, though we have not been collecting the functional status as a variable in our data collection. They were from a population of whom more than 99% are Muslim. Languages spoken in this population are Kurdish and Persian. Almost all were Caucasian and have similar cultural behaviors. Participants who met the inclusion criteria were identified in advance, using the hospitalization records, by an experienced nurse with access to the records. Subjects needed valid contact details to be included. Prior permission was obtained from the director of Imam Ali Hospital, Kermanshah, Iran. Ethics approval for the study was granted by human research ethics committees in Iran (Kermanshah University of Medical Sciences Research Ethics Committee) and Australia (University of Sydney Human Research Ethics Committee); A written informed consent for participation in the study was obtained from all participants.

### Intervention

#### Educational approaches

The intervention included two different educational approaches to training self-care information to patients diagnosed with CHF. One group was trained face-to-face at their homes by CHVs and the second group was trained by a skilled nurse and a general practitioner in three small groups at a conference room in the hospital (Imam Ali Hospital).

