#### Preparing educators

Prior to the intervention ten female CHVs, aged from 27 to 53 years were trained in three workshops by a general practitioner. These subjects were selected from among fifty CHVs connected to a health delivery center (Sameno-al-aemaeh) in Kermanshah. The inclusion criteria were; an acceptable level of conversation skills, ability to speak in Persian and Kurdish, having been actively involved during the preceding year in assisting at the health center and having graduated from high school or beyond. Three one-day workshops were held to train and prepare the selected CHVs, the number and duration of workshops being based on a needs-assessment conducted at the introductory session and using the feedback from participants (CHVs) after that session.

The aim of workshops was to teach the CHVs about the content of the educational programs for patients and how to present the information. The materials were obtained from heart failure text books (Bonow et al.
2011) and related sites (Krum et al.
2011) that have been translated into simple Persian language understandable for patients, even those who might be illiterate. The preparation and simplification was conducted under supervision of a cardiologist. The information was provided in a PowerPoint presentation and in a notebook used in workshops. In addition, during workshops, tutors considered the likely questions or challenging issues that might be faced during their home visits. At the end of the workshops, using role play, each of CHVs was assessed to evaluate her ability as an educator. One of CHVs who did not have an acceptable result was removed from the list. Further, CHVs were given a contact number of a trained general practitioner to ask questions during home visits.

For the second group a nurse and general practitioner both experienced and working in cardiovascular disease and cardiovascular rehabilitation were employed. They were asked to study the notebook prepared as above. They were asked to educate participants, using their own knowledge and considering the aims and objectives of education. They were blind to the study purpose.

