#### Payments

The interventions were started in parallel, though educating by CHVs lasted about two weeks because each CHV had to educate approximately seven to eight patients one-by-one and at their homes. The patients in second group –educated at hospital– were offered reimbursement for travel costs but none asked. Fees were paid to educators of this group, namely, the nurse and general practitioner. CHVs making home visits were reimbursed for travel costs. Taxi fares were paid for one of the investigators who monitored the home-based education. Two months later participants in the three groups were interviewed again at home or hospital, according to their preferences.

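### Education is delivered through shared CHVs and classes, but the named tests treat patients as independent; if outcomes correlate within these units, type I error exceeds 5%

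*Protocol article*

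**What the plan says.** **Delivery.** Under Educational approaches, Group II was "trained by a skilled nurse and a general practitioner in three small groups at a conference room in the hospital". Under Payments, Group I was taught so that "each CHV had to educate approximately seven to eight patients one-by-one and at their homes". Table 1 shows no educator, setting or material for Group III. Under Implementation, 77 individual patients were allocated to each arm.

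**Number of CHVs.** Preparing educators reports ten CHVs trained, then: "One of CHVs who did not have an acceptable result was removed from the list". That leaves nine.

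**Analysis.** Statistical methods names "ANOVA, independent t-test and paired t-test) for assessing differences (between two groups, among three groups and before and after for each group". Rank and median tests are the fallback, and the regression models use patient characteristics such as age, gender, education and disease duration. The section has no term for CHV or class, no random effect and no clustered variance.

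**Sample size.** The inputs are "σ =40, d = 22, Z α/2 = 1.96, Z β =0.1". Neither an ICC nor a design effect appears.

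**The concern.** Patients who share a CHV, or who sit in the same class, may end up with more similar self-care scores than patients who do not. An independent t-test or ANOVA ignores this. It takes the variance of an arm mean as σ²/n, when the variance is larger by the design effect. Clustering is also unequal across arms: many small units in Group I, three large ones in Group II, none in Group III. The three contrasts are therefore affected to different degrees.

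The contrast most exposed is I v II, because both of its arms are clustered. It also carries the study hypothesis that CHVs are equally or more effective than professional educators. An interval that is too narrow could overstate superiority or comparability.

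**Working it through.** **1. The plan's own figure.** The stated size is 60 per group. With σ = 40, d = 22, two-sided 5% and 90% power (z = 1.2816), n = 2 × [40 × (1.96 + 1.2816)/22]² = 69.5, so 70. The plan's 60 is not reproduced. The printed Zβ = 0.1 would give 2 × [40 × 2.06/22]² = 28.06, so 29. Only 80% power (52), multiplied by 1.15, returns 60. That discrepancy is a separate matter. For this point, what counts is that the calculation assumes independence. On that assumption, power at 77 per arm is 92.7%.

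**2. Inputs for clustering.** From the article: 77 per arm, three classes, and ten CHVs less one. Assumed: class sizes 26, 26 and 25; nine CHVs with five loads of 9 and four of 8; ICC 0.01 to 0.10 in the education arms and 0 in control.

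**3. Design effects.** DE = 1 + (Σm²/Σm − 1) × ICC.
- Group I: Σm²/Σm = (5 × 81 + 4 × 64)/77 = 661/77 = 8.58, so DE = 1 + 7.58 × ICC.
- Group II: Σm²/Σm = (2 × 676 + 625)/77 = 1977/77 = 25.68, so DE = 1 + 24.68 × ICC.
- Group III: DE = 1.

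**4. Actual error of the independence test.** True SE / naive SE = r = √[(DEa + DEb)/2]. Actual alpha = 2 × [1 − Φ(1.96/r)].

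With the same ICC in both education arms:

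| ICC | DE, I | DE, II | I v III | II v III | I v II | Power, I v II (d = 22) |
|---|---|---|---|---|---|---|
| 0 | 1.00 | 1.00 | 5.0% | 5.0% | 5.0% | 92.7% |
| 0.01 | 1.08 | 1.25 | 5.4% | 6.4% | 6.9% | 88.6% |
| 0.02 | 1.15 | 1.49 | 5.9% | 7.9% | 8.8% | 84.3% |
| 0.05 | 1.38 | 2.23 | 7.2% | 12.3% | 14.5% | 71.9% |
| 0.10 | 1.76 | 3.47 | 9.5% | 19.0% | 22.5% | 56.0% |

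Example, I v II at ICC 0.05: r = √[(1.379 + 2.234)/2] = 1.344; 1.96/1.344 = 1.458; alpha = 14.5%. The power column uses the true SE with normal critical values, so a small-sample analysis would have less.

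**5. Simulation check.** Simulating the pooled t-test (20,000 runs per cell) gave 5.0%, 7.0%, 9.0%, 14.9% and 22.8% for I v II at the five ICCs, in line with the formula.

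**6. Unequal ICCs.** If the class ICC is 0, Group II has DE = 1 and I v II takes the I v III values: 7.2% at CHV ICC 0.05 and 9.5% at 0.10. With class ICC 0.01 and CHV ICC 0.05, r = √[(1.379 + 1.247)/2] = 1.146 and alpha is about 8.7%.

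**7. CHV count.** 77/9 = 8.6 patients each; 77/10 = 7.7. Nine CHVs at eight each cover 72 of 77, so the stated load fits ten better than nine. With ten CHVs, I v II at a common ICC of 0.05 is 14.2% instead of 14.5%, so the mismatch hardly affects the result.

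**The case against.** - **No ICC is given, and at ICC 0 there is no inflation.** This stands. The claim must be conditional.
- **The three classes had the same nurse, general practitioner and notebook.** Differences between educators therefore cannot create correlation within a class in Group II. Only class dynamics or composition, or drift in what was taught, could do so. This stands, and it matters because the large Group II design effect drives the double-digit figures. In Group I, common workshops, role-play assessment and fidelity checks also aim at uniform delivery, though they do not guarantee it.
- **Patients were randomised individually.** If education changed nobody's score, a comparison with control would keep its 5% level. Inflation against control concerns the null of zero average effect with real variation between units. This limits the I v III and II v III claims.
- **The article is condensed, its tests are introduced as examples, and an analysis plan may exist.** This carries little weight. The article names the tests for its between-group comparisons, and all of them assume independence, which does not fit the delivery it describes.
- **Three classes leave two degrees of freedom for the class variance, so a mixed model is weak where the problem may be largest.** This stands, and it shapes the fix.

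A reader might also infer that having few clusters makes the naive test materially worse than the formula suggests. The simulation does not show this: 14.9% against 14.5% for I v II at ICC 0.05. Few clusters mainly hurt estimation of the variance in a corrected model.

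**Conclusion.** The point holds conditionally. The delivery structure and the independence-based tests are both stated in the article, and for any positive ICC within CHV or class the named tests give standard errors that are too small.

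Under assumed ICCs, nine CHVs and three near-equal classes, a nominal 5% test has an actual error of:
- about 5.4% to 9.5% for I v III (CHV ICC 0.01 to 0.10);
- about 6% to 19% for II v III (class ICC 0.01 to 0.10);
- about 7% to 22% for I v II if both ICCs are equal at 0.01 to 0.10, but only about 7.2% to 9.5% if the class ICC is 0 and the CHV ICC is 0.05 to 0.10.

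A reader might infer that type I error is certainly inflated, or that I v II runs at 14% to 22%. The article supports neither. It reports no correlation, and those figures need a class ICC as high as the CHV ICC although all classes shared their educators and notebook. The CHV count is a minor reconciliation point.

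**What to change.** 1. Retain a CHV identifier for each Group I patient and a class identifier for each Group II patient. The article does not say whether these were recorded; if not, they must be recovered from teaching records.
2. Compare arms with a partially nested mixed model: arm and baseline score as fixed effects, a random CHV effect in Group I, a random class effect in Group II, none in Group III, and small-sample degrees of freedom. SAS, already named, can fit it.
3. Because three classes cannot estimate the class variance reliably, report I v II and II v III over fixed class ICCs from 0 to 0.10.
4. State as a limitation that the effect of the two shared Group II educators cannot be separated from the arm. No model can resolve this.
5. Reconcile the number of CHVs who taught with the patients per CHV, so that the cluster variable is defined.

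**Cost.** Two identifier fields and a different model, with no change to the design. The price is wider intervals, especially for Group II. With σ = 40 and 77 per arm, the naive SE is 40 × √(2/77) = 6.45, a 95% half-width of 12.6 units. For I v II with both ICCs at 0.05 it becomes 1.96 × 6.45 × 1.344 = 17.0. With class ICC 0 and CHV ICC 0.05 it is 1.96 × 6.45 × 1.091 = 13.8. Small-sample degrees of freedom would widen both further.
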